### Sensitivity analysis for the multistate models

If it is decided to withdraw established life-sustaining therapies (e.g., MV) based on the presumed wishes of the patient (e.g., communicated by a surrogate) or the instructions of an advance directive, sedation may be changed to drugs stronger than propofol (midazolam), and opioids (morphine, etc.) are added to analgo-sedate the patient. Death usually occurs one to two days after these therapeutic changes. Consequently, in these cases, the transition from propofol to no propofol would not indicate an improvement in clinical status (as it would otherwise). To account for this bias within the transition from the state "propofol: yes" to the state "propofol: no", we will re-classify the subsequent absorbing state "in-ICU death" into "palliative in-ICU death", if death occurs one or two days after the preceding state transition (time course of states # 1 - 7, Table 3), and into "non-palliative death" in all other time courses of states.

**Table 3 t3:** Survey of time courses of different daily states used to re-define the absorbing state "in-intensive care unit death" into "palliative in-intensive care unit death" (time course of states #1 to #9) and "non-palliative in-intensive care unit death" (all other time courses)

Time course of states #	State on day x minus n (n > 2)	State on day x minus 2	State on day x minus 1	Initial state (day x)	Absorbing state (day x plus 1)
1	Any	Any	"Propofol: yes" "MV: yes"	"Propofol: no" "MV: yes"	In-ICU death
2	Any	Any	"Propofol: yes" "MV: no"	"Propofol: no" "MV: no"	In-ICU death
3	Any	Any	"Propofol: yes" "MV: yes"	"Propofol: no" "MV: no"	In-ICU death
4	Any	"Propofol: yes" "MV: yes"	"Propofol: no" "MV: yes"	"Propofol: no" "MV: yes"	In-ICU death
5	Any	"Propofol: yes" "MV: no"	"Propofol: no" "MV: no"	"Propofol: no" "MV: no"	In-ICU death
6	Any	"Propofol: yes" "MV: yes"	"Propofol: no" "MV: yes"	"Propofol: no" "MV: no"	In-ICU death
7	Any	"Propofol: yes" "MV: yes"	"Propofol: no" "MV: no"	"Propofol: no" "MV: no"	In-ICU death
8	Any	Any	"Propofol: no" "MV: no"	"Propofol: yes" "MV: no"	In-ICU death
9	Any	"Propofol: no" "MV: no"	"Propofol: yes" "MV: no"	"Propofol: yes" "MV: no"	In-ICU death

MV - mechanical ventilation; ICU - intensive care unit.

If it is decided to either terminate supporting therapies or, based on the presumed wishes of the patient (e.g., communicated by a surrogate) or on an advance directive, not to start or to increase life-sustaining therapies (e.g., oxygen supply), propofol may be started for sedation. Death usually occurs one to two days after these therapeutic changes. To account for this bias within the transition from the state "propofol: no" to the absorbing state "propofol: yes", we will re-classify the subsequent absorbing state "in-ICU death" into "palliative in-ICU death", if death occurs one or two days after the preceding state transition (time course of states # 8 - 9, Table 3), and into "non-palliative death" in all other time courses of states.

For the reasons described in b), the preexisting propofol dose can be increased acutely to relieve symptoms. Therefore, when analyzing transitions to the absorbing ‘in-ICU death’ state in the combination with a certain preceding propofol-associated energy intake in the initial state, we will re-define the absorbing state "in-ICU death" into "palliative in-ICU death", if there is a significant increase of propofol-associated energy intake from one day to the other ([propofol-associated energy intake on transition day minus energy intake on the day before transition day]/energy intake on the day before transition day = > 100%), or if propofol-associated energy intake on transition day is > 4.5kcal/kg day, and into "non-palliative death" with all other changes/intake.

Consequently, depending on each patient's history, these sensitivity analyses will increase the number of possible state transitions (Figure 2) compared to the primary analysis (Figure 1).

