### Research question

The average causal effect of propofol on the risk of in-hospital all-cause death has been demonstrated in previous clinical trials. Associations between propofol doses, timing, and responses, however, are unknown. The present study aims to fill this gap. The primary research question focuses on the association between defined levels of propofol-associated energy intake in the early and late phases following ICU admission and competing risks (time to discharge alive (being a surrogate of morbidity), and in-hospital death, respectively). The secondary research question centers on the association between preceding cumulated or daily propofol energy intake, or the number of days on propofol prior to transitioning from propofol to, e.g., death or being free of propofol the day after transitioning. These factors will be examined in terms of measured variables and transition probabilities, while accounting for bias from confounding by indication or palliative care. The general aim is to provide more evidence on safe propofol dosing and duration.

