### Outcome measures

–**Primary outcomes:** time-to-hospital discharge-alive as a surrogate of morbidity, and to in-hospital death (adjusted hazard ratios and 95% confidence intervals [95%CI]).Adjusted hazard ratios compare two levels of daily propofol-associated energy intake. They will be calculated separately for each day after ICU admission using sub-distributional and cause-specific hazard models. The observation period will start on the day of ICU admission, and events (day of discharge alive/in-hospital death) will be registered from day 2 after ICU admission until the end of the lead-time (defined as twice the number of days that a patient received propofol therapy).–**Secondary outcomes:** the risk of state transition (adjusted hazard ratio and 95%CI) and the transition probabilities between the different states (Figure 1).State transition risks and probabilities will be referred to a certain amount of propofol-associated energy intake or a specific duration of propofol therapy; adjusted hazard ratios will be calculated for all 17 transitions (Figure 1). State transition will be registered until day 13 after ICU admission. Initial and absorbing states include "propofol: no/MV: no", "propofol: yes/MV: no", "propofol: no/MV: yes", "propofol: yes/MV: yes", post-transition absorbing states include "in-ICU death" and "ICU discharge alive.

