Hazard ratios can be used to describe the association of covariates and exposures with each transition (e.g., from alive to death in the ICU). In multistate settings, separate hazards are estimated for each possible transition. These individual transition hazards are then combined to obtain the overall transition probabilities by calculating the empirical transition matrix. While hazard ratios describe the direct effect on the instantaneous risk of a transition (relative risk), transition probabilities depend on the hazards of all possible transitions (absolute risk). Together, these two quantities provide a comprehensive interpretation of the underlying processes.

A particular focus will be on the concomitant use of MV, which is one of the main reasons for propofol use in critically ill patients and therefore the most important confounder of propofol-associated outcomes. The time-dependent confounder MV is considered as a separate state^(27)^ in the multistate model (Figure 1). This has the advantage that the transitions to the absorbing states "ICU discharge alive" and "in-ICU-death", and thus the transition probabilities to these states, can be modelled separately, depending on the current time-dependent propofol status (yes or no), but also on the subject-specific history of MV treatment and propofol administration (number of days with propofol therapy, cumulated propofol-associated energy intake). As the model is conditional on propofol status at any given time, but the frequency of MV use may vary between subjects within each propofol state, it allows the association of propofol and MV status with outcomes to be disentangled.

Results for the association between the exposure variables preceding transition (number of days with propofol therapy, cumulated propofol-associated energy intake (kcal/kg), propofol-associated energy intake (kcal/kg day) on transition day), and transition risk will be presented as adjusted hazard ratios (with 95%CIs) and adjusted transition probabilities (with 95%CIs) depending on a specific day after ICU admission (Days 1 to 11).

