### Sensitivity analyses accounting for palliative care bias/confounding by indication

To account for palliative care bias in the multistate models and analysis of time-to-discharge alive/in-hospital death, a sensitivity analysis is required concerning patients with an early death after termination or beginning of propofol therapy (< 48 hours after the last day of propofol therapy). Palliative care bias arises if physicians modify therapy not for medical reasons but because of end-of-life decisions. Several scenarios are possible (Table 2):

**Table 2 t2:** Survey of sensitivity analyses that account for bias relating to indications and palliative care

	Primary outcome	Secondary outcome		
Outcome measures	Time-to-discharge-alive/in-hospital death	Hazard of state transition		
Exposure variables	Categorized daily propofol-associated energy intake (kcal/kg and day)	Number of days with propofol therapy preceding transition day	Cumulated amount of PAEI (kcal/kg) before state transition (initial state: propofol "yes")	Amount of daily PAEI (kcal/kg and day) on transition day (initial state: propofol "yes")
Sensitivity analyses	Use of a lag time of two days after the last day of propofol therapy	Re-definition of the absorbing state "in-ICU death" into "palliative in-ICU death" (for time courses of different daily states #1 to #9, Table 3) and "non-palliative in-ICU death" (all other state time series)	Re-definition of the absorbing state "in-ICU death" into "palliative in-ICU death" (if [PAEI on transition day minus PAEI on the day before transition day]/PAEI on the day before transition day ≥ 100%) and "non-palliative in-ICU death" (all other changes)	Re-definition of the absorbing state "in-ICU death" into "palliative in-ICU death" (if PAEI on transition day > 4.5kcal/kg day) and "non-palliative in-ICU death" (all other intake)

PAEI - propofol-associated energy intake; ICU - intensive care unit.

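### The palliative-care sensitivity analysis splits only the later ICU death, so it cannot test the stop-propofol and start-propofol hazard ratios by number of propofol days that it is said to correct

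*Protocol article*

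**What the plan says.** The section *Sensitivity analysis for the multistate models* begins with end-of-life decisions in which propofol is replaced by other drugs. In those cases, it says, "the transition from propofol to no propofol would not indicate an improvement in clinical status (as it would otherwise". The aim follows: "To account for this bias within the transition from the state 'propofol: yes' to the state 'propofol: no". The action in the same sentence is: "we will re-classify the subsequent absorbing state 'in-ICU death' into 'palliative in-ICU death', if death occurs one or two days after the preceding state transition", using time courses #1 to #7 of Table 3. A later paragraph of that section repeats the construction for starting propofol, with courses #8 and #9.

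For the exposure 'number of propofol days', Table 2 gives the same single action: "Re-definition of the absorbing state 'in-ICU death' into 'palliative in-ICU death' (for time courses of different daily states #1 to #9, Table 3". For the other two exposures (cumulated intake and intake on the transition day), Table 2 uses different triggers: a rise of at least 100%, or an intake above 4.5 kcal/kg per day. The text limits those two rules to analyses of transitions into ICU death.

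Four other statements bear on the point:
- *Overall design of the multistate models*: "In multistate settings, separate hazards are estimated for each possible transition".
- *Outcome measures*: "adjusted hazard ratios will be calculated for all 17 transitions (Figure 1".
- *Research question* names "being free of propofol the day after transitioning" among the transitions of interest.
- *Limitations* says that sensitivity analyses will leave out suspicious transitions and events close to the last propofol day.

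**The concern.** The protocol places the bias in one transition and changes another. If some moves from propofol to no propofol are end-of-life withdrawals, the hazard ratio for that move mixes recovery with its opposite. A sensitivity analysis should show how far the estimate depends on those moves. The planned one leaves all of them in the event count.

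The move off propofol has its own reported hazard ratio and is part of the secondary research question. Readers who see the same estimate in both analyses, with text saying that palliative bias within this transition was accounted for, would naturally take the agreement as reassurance. It would carry no information on that question. The same applies to starting propofol.

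**Working it through.** **1. Which events the rule touches.** In a piecewise exponential model with a separate hazard for each transition, the log-likelihood for a move from state a to state b is a sum over patient-days spent in a:

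sum of [ d_ab × log(λ_ab) − λ_ab × t ]

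Here d_ab marks an a-to-b event and t is time at risk in a. Only days in a, a-to-b events and covariates enter. Table 3 shows where the propofol move and the relabelled event fall:

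| Table 3 courses | Propofol move | Step of that move | Relabelled event |
|---|---|---|---|
| #1 to #3 | yes to no | day x−1 to x | 'propofol: no' to death, x to x+1 |
| #4 to #7 | yes to no | day x−2 to x−1 | 'propofol: no' to death, x to x+1 |
| #8 | no to yes | day x−1 to x | 'propofol: yes' to death, x to x+1 |
| #9 | no to yes | day x−2 to x−1 | 'propofol: yes' to death, x to x+1 |

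In every course the propofol move comes before the relabelled event and belongs to a different transition. The split changes d only for transitions into death. It changes neither the events, nor the days at risk, nor the number of propofol days for the moves between propofol states.

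**2. How exact this is.** If each hazard is fitted on its own, the two hazard ratios are equal. The article says that hazards are separate, not that the fits are, and all models carry an ICU random effect. If terms were shared across transitions in one joint fit, small differences could arise. 'Essentially unchanged' is the safe statement.

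**3. Simulated illustration.** All hazards are assumed; none comes from the document. There were 18,000 patients over days 0 to 11, in a simplified propofol on/off model without mechanical ventilation. The hazard of stopping was regressed on propofol days, with three levels of end-of-life withdrawal.

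| Quantity | Low | Middle | High |
|---|---|---|---|
| Stop events, death merged | 15,592 | 16,347 | 16,893 |
| Stop events, death split as planned | 15,592 | 16,347 | 16,893 |
| HR per propofol day, merged | 1.000 | 1.026 | 1.056 |
| HR per propofol day, split as planned | 1.000 | 1.026 | 1.056 |
| HR with stops before a palliative death coded apart | 0.975 | 0.981 | 0.980 |
| Deaths from the off state, all | 3,453 | 5,481 | 7,924 |
| Of these, still non-palliative after the split | 547 | 769 | 1,029 |

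The split does a great deal for the death hazard and nothing for the stop hazard. The simulated recovery hazard fell by exp(−0.05) = 0.951 per propofol day. Coding the suspect moves apart brings the estimate closer to that value but does not reach it, because withdrawals with no recorded death within two days stay in.

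**4. Size.** The document gives neither the number of stop moves nor the palliative share. For illustration, assume 18,000 patients, 10–15% ICU death, 20–40% of these deaths in courses #1 to #7, and 11,000 stop moves:
- 18,000 × 0.10 × 0.20 = 360, and 360/11,000 = 3.3%.
- 18,000 × 0.15 × 0.40 = 1,080, and 1,080/11,000 = 9.8%.

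With reported HR = (1 − p) × HR for recovery + p × HR for withdrawal, a recovery HR of 1.00 and a withdrawal HR of 1.5 to 2.0, the result runs from 0.967 × 1.00 + 0.033 × 1.5 = 1.02 to 0.902 × 1.00 + 0.098 × 2.0 = 1.10. The simulation used much larger shares: (3,453 − 547)/15,592 = 19% up to (7,924 − 1,029)/16,893 = 41%. Its high setting has 7,924/18,000 = 44% dying from the off state, which does not fit the roughly 70% discharged alive given under *Sample size considerations*. Neither range is an estimate for this database.

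**5. The Limitations statement.** Tables 2 and 3 and the surrounding text contain relabelling of deaths and, for the competing risk models, a two-day lag. Nothing there drops, censors or recodes a move between propofol states.

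**The case against.** **The split has a proper use.** Labelling a death by the patient's past is legitimate in a multistate model, and it separates palliative from other deaths in the hazards into death, a main concern of the study. This stands. A reader might infer that the palliative sensitivity analysis is worthless; the documents do not support that.

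**The claim made for it is narrow.** A reader might extend the point to all three exposures. Table 2 ties courses #1 to #9 to the number of propofol days only, and the rules for the two intake exposures claim to inform only transitions into death. This stands, so the point is confined to the number-of-days exposure.

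**The Limitations section mentions exclusion, and Figure 2 is not visible.** A reader might conclude that no check was intended. The Limitations wording suggests that one was, but no rule carries it out. The figure could in principle show more, but splitting the death state already accounts for the added transitions that the text mentions, and Tables 2 and 3 define nothing else. What remains is an inconsistency to be reconciled.

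**The remedy conditions on the future.** Labelling a stop by whether death follows also removes non-palliative early deaths. Suppose there are no palliative withdrawals, the true HR is 1.00, and death within two days of stopping is 5% at one exposure level and 10% at another (assumed figures). The recoded analysis then gives 0.90/0.95 = 0.95. This stands. It limits the recoded result to a sensitivity analysis of a different quantity.

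**Conclusion.** The point holds for the hazard ratios of stopping and starting propofol by number of propofol days. The protocol says that it accounts for palliative bias within these moves, yet the stated rule alters only the hazards into death. Given separately estimated transition hazards, the two sets of hazard ratios agree by construction: exactly with separate fits, nearly so otherwise. Their agreement cannot support a claim of robustness.

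A reader might also infer a definite bias, such as a hazard ratio shifted by 0.02 to 0.10. The documents give no palliative share, no count of moves and no withdrawal effect, so neither size nor direction can be stated. The matter concerns a secondary outcome and one set of sensitivity analyses. It should be corrected before analysis, but it does not touch the primary competing risk analysis.

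**What to change.** 1. Keep the split of in-ICU death for the hazards into death.
2. For the number-of-days exposure, add a sensitivity analysis. Code a yes-to-no move that starts courses #1 to #7, and a no-to-yes move that starts courses #8 or #9, as a separate transition type. Leave the risk set unchanged and re-estimate the hazard ratios for the remaining moves.
3. Report it as a changed estimand: a move not followed by ICU death within two days. Disclose that the label uses later outcome, also captures non-palliative early deaths, and cannot classify moves near the end of state recording.
4. State in *Sensitivity analysis for the multistate models* (both the stopping and the starting paragraph) and in *Limitations* that the death split alone informs only the hazards into death. Align the Limitations wording on excluded transitions with what will be done.

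The cost is a recoding of daily states already in the database, using Table 3's own courses, and one more set of model fits. The price is interpretive: the new estimate has its own selection effect and should stand beside the main one, not replace it.

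### Table 3 has no time course for propofol started together with, or the day before, ventilator withdrawal, so such deaths default to non-palliative although the text's own scenario describes them

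*Protocol article*

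**What the plan says.** States are written below as propofol/MV, so no/yes means off propofol and on MV. Day x is the last day before death, and death falls on day x+1.

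In the protocol article, section 'Sensitivity analysis for the multistate models', in-ICU death is split into a palliative and a non-palliative form.

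- **Stopping propofol.** The scenario is a decision to "withdraw established life-sustaining therapies (e.g., MV) based on the presumed wishes of the patient", with sedation moved from propofol to other drugs. Rows 1 to 7 of Table 3 apply.
- **Starting propofol.** The scenario opens with "If it is decided to either terminate supporting therapies or, based on the presumed wishes of the patient" (among other grounds), therapy is not started or not increased. Then "propofol may be started for sedation". The rule is introduced with "To account for this bias within the transition from the state 'propofol: no' to the absorbing state 'propofol: yes" and carries no MV condition in words. It applies "if death occurs one or two days after the preceding state transition (time course of states # 8 - 9, Table 3").
- **Default.** The Table 3 caption assigns everything unlisted to "non-palliative in-intensive care unit death' (all other time courses").

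Row 8 is any state on day x-2, no/no on day x-1 and yes/no on day x. Row 9 is no/no, yes/no, yes/no. In Table 2, the Table 3 courses are the only rule for the exposure 'number of days with propofol therapy'. The two energy-intake exposures use dose-based rules instead.

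**The concern.** The text describes propofol being started when supporting therapy is ended, and MV is the article's own example of a therapy that is withdrawn. The natural daily record of that event in a ventilated patient is no/yes followed by yes/no, or no/yes, yes/yes, yes/no if propofol starts a day ahead. Rows 8 and 9 admit neither. The article calls MV the most important confounder, and its Limitations section relies on these sensitivity analyses to reduce end-of-life bias. If deaths of this kind stay labelled non-palliative, the hazard of non-palliative death from the yes/no state still contains some of the deaths that the analysis was designed to remove.

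**Working it through.** No sample size or power figure is involved. The check compares the rows of Table 3 with the scenarios in the text and then counts patterns.

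**Step 1. Mirror the stop rows.** Replace 'propofol stopped' by 'propofol started' in each Table 3 course in which MV is withdrawn:

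| Pattern before death | Propofol stopped | Listed | Propofol started | Listed |
|---|---|---|---|---|
| Both changes on day x | yes/yes, no/no | row 3 | no/yes, yes/no | no |
| Propofol changes on day x-1, MV withdrawn on day x | yes/yes, no/yes, no/no | row 6 | no/yes, yes/yes, yes/no | no |
| Both changes on day x-1 | yes/yes, no/no, no/no | row 7 | no/yes, yes/no, yes/no | no |

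In all three start courses death comes one or two days after propofol starts, so they fall inside the time window that the text sets.

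**Step 2. Count the histories ending in yes/no.** Four states on days x-2, x-1 and x give 4 × 4 × 4 = 64 histories, of which 4 × 4 = 16 end in yes/no.

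- Classed palliative: 4 by row 8 (any state on day x-2) plus 1 by row 9 = 5.
- Classed non-palliative by default: 16 − 5 = 11.
- Histories with MV going from yes to no within the window: 12. Row 8 catches 2 of these (yes/yes or no/yes on day x-2, then no/no, then yes/no). The other 12 − 2 = 10 are among the 11 defaults.
- Of the 12, propofol is started within the window in 9 (2 caught, 7 missed) and is on throughout in 3 (none caught).

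**Step 3. What the three added courses would catch.** No/yes, yes/no with any state on day x-2 gives 4 histories, and the other two courses give 1 each: 4 + 1 + 1 = 6 of the 7 missed. The total becomes 2 + 6 = 8 of 9. The one left over is no/no, yes/yes, yes/no, where MV itself began inside the window. Its stop counterpart (yes/no, no/yes, no/no) is also unlisted, so leaving it out keeps the two directions alike.

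**Step 4. Where the gap acts.** For the number-of-days exposure nothing but Table 3 re-labels deaths. The primary outcome uses a two-day lag instead and is not touched.

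These are counts of possible patterns, not of patients. The article gives no frequencies.

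**The case against.** **The text defers to the table.** The start rule is tied to rows 8 and 9 and sends all other courses to non-palliative. Its only worked example is oxygen supply, which suits unventilated patients, and MV is named only in the stopping scenario. A reader might infer that every start of propofol within two days of death must be palliative. On that reading Table 3 captures 5 of 24 histories. The article does not support this, because the rule is limited to the listed rows and no scenario describes starting propofol while MV simply continues. What does not fall away is that the starting scenario names termination of supporting therapies, and the listed rows leave out its most direct form in a ventilated patient.

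**Row 8 is wider than it looks.** Its open cell on day x-2 catches patients ventilated two days earlier. This stands: rows 8 and 9 are not confined to never-ventilated patients, and the gap is limited to propofol started together with, or the day before, withdrawal.

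**Propofol continued through withdrawal.** A reader might count yes/yes, yes/no, death as a further omission. The section on palliative care bias restricts the exercise to death soon after propofol is ended or begun. The only scenario for existing propofol is an acute increase, handled by dose rules for the energy-intake exposures. Unchanged propofol is outside the described scenarios.

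**Figure 1 is not shown.** Four transient and two absorbing states allow 4 × 3 + 4 × 2 = 20 transitions, and the article models 17. Whether a direct no/yes to yes/no move is among them cannot be checked. The course no/yes, yes/yes, yes/no needs no such move and is missed too.

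**Direction of bias.** A reader might infer that the analysis is tilted towards harm from propofol, or attach a multiplier to the hazard. Neither is supported. Retained deaths can only raise the non-palliative hazard from yes/no, but the reported hazard ratio is per day of prior propofol. Its shift depends on how many propofol days those patients had, which is not given.

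**Conclusion.** The point holds in narrow form. The starting scenario and rows 8 and 9 do not match: three courses that fit the scenario and its time window default to non-palliative, while their counterparts for stopping propofol are all listed (3 of 3 against 0 of 3). This can leave end-of-life deaths in the non-palliative hazard from the state with propofol and without MV.

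The conclusion rests on reading supporting therapies in the starting paragraph as including MV, as the stopping paragraph does for life-sustaining therapies. The scope is one exposure, in a sensitivity analysis of the secondary outcome. The number of deaths involved is unknown, and the effect on the per-day hazard ratio is not determined. It should be corrected, but it does not threaten the primary analysis.

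**What to change.** Before outcomes are analysed, reconcile the starting paragraph with Table 3. Add these courses as palliative in-ICU death:

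1. no/yes, yes/no, death (any state on day x-2)
2. no/yes, yes/yes, yes/no, death
3. no/yes, yes/no, yes/no, death

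Then update the reference to rows 8 to 9 in the text, and to rows 1 to 9 in Table 2 and the Table 3 caption. If the omission is intended, say so and give the reason. Courses with propofol unchanged through MV withdrawal could be run as an optional further sensitivity check, labelled as going beyond the described scenarios.

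The cost is three table rows and a recoding of daily states already in the database. The downside is that some non-palliative deaths soon after extubation would be labelled palliative, as already happens with rows 3, 6 and 7. Only death labels change. Settling them before outcomes are seen avoids a data-dependent choice.
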